### Statistical methods

Data will be analyzed by using R studio 4.2.2 for Windows (Armonk, NY, United States). Data from the primary outcome will be presented as mean ± standard deviation if normally distributed, and t-test will be conducted; otherwise, the data will be reported as median (IQR), and no-parametric tests will be performed. Categorical data will be summarized as frequencies (percentages) and compared between study groups using χ2 tests or Fisher exact tests, as appropriate. *P* value < 0.05 was considered significant.

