## Background

Since Transvaginal Natural Orifice Transluminal Endoscopic Surgery (vNOTES) was applied and reported in 2007 by Marescaux et al., this technique has been increasingly conducted in the field of gynecology, such as hysterectomy [1, 2], adnexectomy [3], and myomectomy [3, 4]. Published literature has proved that, compared to traditional laparoscopic surgery, vNOTES hysterectomy is associated with a lower pain score after surgery and a shorter length of hospital stay [1]. Due to its minimally invasive and without abdominal incisions, maximum aesthetics can be achieved.

During the routine vNOTES procedure, carbon dioxide (CO_2_) pneumoperitoneum is required. CO2 insufflation may induce hemodynamic instability and acid–base imbalance. A well-summarized review has reported that acidosis, inflammation, oxidative stress, and hypothermia may all be associated with CO_2_ pneumoperitoneum [5]. Moreover, in an animal study, the authors found that an inflammatory response was evoked during pneumoperitoneum [6]. Additionally, the transvaginal insertion of devices to establish CO_2_ pneumoperitoneum makes the already narrow surgical space even more crowded, further exacerbating the inconvenience of transvaginal operations [7]. In 2014, Chen et al. performed the first transvaginal appendectomy under gasless laparoscopy [7]. Subsequently, they reported that transvaginal salpingo-oophorectomy with gasless laparoscopy was successfully conducted in ten patients [8]. However, technical difficulties associated with gasless laparoscopy, such as limited abdominal space and poor surgical visualization restrict its application.

To date, literature regarding the advantages of gasless vNOTES is insufficient. Most studies related to gasless vNOTES are case series, which is not convincing enough. Thus, the aim of our study is to compare gasless vNOTES vs. traditional vNOTES on hemodynamic profiles and outcomes in patients with benign gynecological disease. The primary outcome is the changes in mean arterial pressure (MAP) and heart rate (HR) at different time points during the surgery. The secondary outcomes will be surgical conversion rate and complications. We hypothesize that compared with those in the traditional vNOTES group, hemodynamic profiles will be changed less during gasless vNOTES, while safety can be promised.

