### Data collection

The following data will be collected during the study. To guarantee the study quality, all the investigators will be trained and pass the examinations. The trained investigator (YW) who will be blinded to the allocation will collect intraoperative data. KL, QH, and QZ will do the anesthesia procedures and collect intraoperative data, respectively; to avoid bias, they will not participate in postoperative data collection. All the statistical analyses will be performed by one of the corresponding authors (YC).Demographic data: Age, BMI, ASA status, clinical diagnosis, history of spontaneous delivery, abdominal surgery history, and surgical index.Intraoperative data: The MAP and HR prior to induction (T0), at the time point of intubation (T1), 10 min after tracheal intubation (T2), surgical incision immediately (T3), 10 min after surgical incision (T4), 10 min before the end of surgery (T5), at the end of surgery (T6), and at the time point of tracheal extubation (T7); duration of surgery; duration of anesthesia; the consumption of anesthetics (including sufentanil and cisatricurium); consumption of vasoactive drugs (including nitroglycerin and metaraminol); intraoperative estimated blood loss. Intraoperative complications include bowel, ureter, and bladder injury.Postoperative data*Postoperative pain assessment* All patients will be guided to use a 0 to 10 cm visual analogue Scale (VAS) to express the degree of pain. VAS scores are collected at the time of 2 h after surgery and 24 h after surgery. Additional analgesic medications are available at the patient’s request. Number of patients who have a requirement for rescue analgesia are recorded. Postoperative rescue analgesia can be provided by intravenous injection of 5 μg sufentanil or ketorolac 30 mg.*Postoperative adverse events *The incidence of postoperative nausea and vomiting (PONV) during postoperative 24 h are recorded. Nausea is referred to the patient with uncomfortable feeling in their stomach, and the severity of nausea is evaluated as follows*:* none = 0, mild = 1, moderate = 2*.* If there is gastric content vomited out, it is scored as 3. Rescue antiemetic could be offered to any patient who has a nausea score > 2. Postoperative complications include surgical site infection within 14 days, and unplanned secondary surgery related to this surgery.

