### Outcome measures

1. The primary outcome is vital signs at the different time points, including before anesthesia (baseline: T0), at endotracheal intubation (T1), 10 min after endotracheal intubation (T2), at the beginning of the operation (T3), 10 min after the operation (T4), 10 min before the end of the operation (T5), at the end of the operation (T6) and at the time of tracheal extubation (T7).2. The second outcomes are collected as follows.①Surgical conversion rate refers to the surgeon cannot complete the surgery in the scheduled mode of operation, and has to convert to open abdominal surgery or traditional multiport laparoscopic surgery, or single port laparoscopic surgery. For the patient who is allocated to the gasless vNOTES group, the surgeon requires the use of traditional vNOTES with CO_2_ pneumoperitoneum if they are unable to complete the surgery under gasless vNOTES, and this patient is considered as a surgical conversion. If the operation cannot be completed according to the scheduled surgical method, the surgical strategy can be changed as appropriate.② Duration of surgery (from speculum placement to suturing the wound)③ Duration of anesthesia (from anesthesia induction to endotracheal extubation)④ The anesthetic consumption during the surgery, including sufentanil and cisatracurium⑤ Intraoperative estimated blood loss⑥ VAS and PONV scores at postoperative 2 h and 24 h.⑦ Administration of vasopressor drugs from the beginning of general anesthesia induction to 15 min after endotracheal intubation, including times, dosage, and type.⑧ Intraoperative and postoperative complications (e.g., bowel, ureter, and bladder injury, surgical site infection, and unplanned secondary surgery).⑨ Time of first getting out of bed after surgery⑩ Time of first eating after surgery after surgery, including light drink.

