### Sample size estimation

The sample size calculation was based on the changes in patients' blood pressure at the beginning of surgery. Since no similar studies have been conducted before, a pilot study was conducted previously. According to the results of the pilot study, in the traditional vNOTES group, 50% of patients had a greater than 20% change in blood pressure at the beginning of the CO_2_ pneumoperitoneum. Due to the different surgical strategies, CO_2_ pneumoperitoneum is not required in the gasless vNOTES group. We assume that the number of patients with a blood pressure change of more than 20% is less in the gasless vNOTES group than in the traditional vNOTES group. The 10% reduction in the gasless vNOTES group was considered to be statistically significant. A statistical power of 80% and a one-sided α significance level of 0.05 were used for power analysis with 1:1 allocation. A sample size of 49 patients in each arm was estimated. Considering a dropout rate of 20%, 60 patients for each group were enrolled.

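### The primary outcome is MAP and HR at eight time points, tested at P < 0.05 with no single primary contrast and no multiplicity control

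*Protocol article*

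**What the plan says.** The Background section defines the outcome as changes in two variables: "The primary outcome is the changes in mean arterial pressure (MAP) and heart rate (HR) at different time points during the surgery". The Outcome measures section describes values at listed times instead: "The primary outcome is vital signs at the different time points, including before anesthesia (baseline: T0", continuing to T7 at extubation. The Data collection section confirms that both variables are recorded at all eight times ("The MAP and HR prior to induction (T0), at the time point of intubation (T1", and so on to T7).

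The Statistical methods section gives the whole primary analysis: "Data from the primary outcome will be presented as mean ± standard deviation if normally distributed, and t-test will be conducted", with a non-parametric test if the data are not normal. Its significance rule is a P "value < 0.05 was considered significant". None of these sections names a primary time point, a primary variable, a summary over time, a baseline covariate or a multiplicity rule.

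The sample size section looks at a single moment ("The sample size calculation was based on the changes in patients' blood pressure at the beginning of surgery") and a yes/no endpoint, the proportion of patients with more than a 20% change in blood pressure. Neither definition of the primary outcome uses that endpoint.

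**The concern.** A t-test compares one variable at one time. Applied to two variables at eight times, with no summary measure, it becomes a family of up to 16 primary tests, each at 0.05. The Discussion says that a favourable haemodynamic and safety result would make gasless vNOTES an optimal option. Under the stated rule, one nominal P value among many could supply the haemodynamic half of that claim.

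Several of the tests cannot show the effect of interest. T0, T1 and T2 precede the operation, so a significant difference there would not be an effect of pneumoperitoneum or lifting. They nevertheless stand equal with the later times in the primary outcome.

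A second, smaller matter is T0. If levels are compared, the baseline reading is unused. If changes from T0 are compared, it is used, but not in the most precise way. The text does not settle which is meant.

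**Working it through.** **Inputs from the protocol article.** Two variables (Background; Data collection). Eight times, T0 to T7, with T0 the baseline (Outcome measures). Significance level 0.05 per test (Statistical methods); its sidedness is not stated, and two-sided is assumed here. The article states no familywise error rate, so there is no figure of its own to reproduce.

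**Assumed inputs.** The article gives no correlations. Between time points within a variable, an equal correlation r of 0.3, 0.5 or 0.7 is assumed. MAP and HR are taken as independent of each other.

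**Step 1: number of tests.** T0 to T7: 2 × 8 = 16. Without the T0 comparison: 2 × 7 = 14. T4 to T7 only: 2 × 4 = 8.

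**Step 2: independent tests.** The chance of at least one false positive among m tests is 1 − 0.95^m. The chance of at least one in the direction favouring gasless vNOTES is 1 − 0.975^m.

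- m = 14: 1 − 0.95^14 = 51.2%; favourable only, 1 − 0.975^14 = 29.8%
- m = 8: 1 − 0.95^8 = 33.7%; favourable only, 1 − 0.975^8 = 18.3%

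**Step 3: correlated tests.** Test statistics were simulated as multivariate normal under no effect, in two independent blocks with equal correlation r inside each block.

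| Times tested, both variables | r = 0.3 | r = 0.5 | r = 0.7 |
|---|---|---|---|
| T1–T7, either direction | 47% | 41% | 32.5% |
| T4–T7, either direction | 32% | 29% | 24% |
| T1–T7, favourable only | 26% | 22% | 17% |
| T4–T7, favourable only | 17% | 15% | 13% |

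A correlation of 0.3 between MAP and HR lowers the either-direction figures by about one percentage point. The benchmark is 5% for the either-direction rows and 2.5% for the favourable-only rows.

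**Step 4: use of T0.** Let r now be the correlation of T0 with a later reading, and assume equal variances at the two times. Relative to a test on levels (variance 1), a change score has variance 2(1 − r), and adjustment for T0 by analysis of covariance has 1 − r².

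| r (assumed) | Levels | Change score | Adjusted for T0 |
|---|---|---|---|
| 0.3 | 1 | 1.40 | 0.91 |
| 0.5 | 1 | 1.00 | 0.75 |
| 0.7 | 1 | 0.60 | 0.51 |

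Adjustment has the smallest variance in every row.

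**The case against.** The strongest reply is that the article never says the tests are run separately at each time, and that a condensed article may leave longitudinal modelling and covariates to an analysis plan that is not shown. The first part is correct: separate tests are an inference, though a strong one, because a t-test fits nothing else in the outcome as defined. The second part excuses missing detail. It does not cover this point, because the article does state a primary test and a significance rule, and they do not fit the outcome it states.

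A reader might put the error rate at 56%, from 1 − 0.95^16. That counts the T0 comparison, which is not a treatment effect, and assumes independence between repeated readings in the same patient. It should not be the headline. Nor would any significant result support the hypothesis, which is directional: haemodynamics change less with gasless surgery. This is why the favourable-only figures are given.

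A reader might also infer that the plan ignores the measured baseline. The document does not support that. The Background section speaks of changes, and the Outcome measures section labels T0 as baseline, so a t-test on change from T0 is compatible with the text. Nor is an unadjusted comparison invalid: in a randomised trial the nominal error rate already allows for chance imbalance. What stands is that the two sections disagree, and that adjustment would be more precise.

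Finally, the sample size section does point to one contrast at one moment. That contrast is not carried into the outcome definition or the analysis, so it does not limit the number of primary tests.

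**Conclusion.** The multiplicity gap is real and concerns the trial's main conclusion. On the natural reading of the plan, the chance of at least one false-positive primary result over T1 to T7 is 51% under independence and about 33 to 47% at r = 0.7 to 0.3. Restricting to T4 to T7 still leaves about 24 to 34%. Counting only results favouring gasless vNOTES gives about 13 to 30% across both sets of times, against 2.5%. The exact figure depends on correlations that the protocol does not give. The conclusion does not: every case examined is several times the nominal rate.

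The baseline issue is secondary. It is an inconsistency between changes and levels plus some avoidable loss of precision, whose size rests wholly on an assumed correlation.

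**What to change.** Before any unblinded analysis, amend the Outcome measures and Statistical methods sections as follows.

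- Name one primary contrast: the difference between arms in MAP over the times after pneumoperitoneum or lifting begins (T4 to T6). Estimate it from one repeated-measures mixed model with arm, time, arm × time and T0 MAP as covariate, tested at two-sided 0.05.
- Test HR in the same way, with T0 HR as covariate, only if the MAP contrast is significant.
- Report individual time points as estimates with 95% confidence intervals and no significance claims.
- Use one description of the outcome throughout. With T0 as a covariate, the choice between change and level no longer alters the estimated difference between arms.
- Do not adjust for T3 unless it is confirmed to precede CO2 insufflation in every patient. The sample size section speaks of the beginning of surgery, yet takes its pilot rate ("50% of patients had a greater than 20% change in blood pressure at the beginning of the CO_2_ pneumoperitoneum") from the start of insufflation, as if the two were one moment. T3 may therefore be affected by treatment, and adjusting for it could remove part of the effect.

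One contrast holds the error at 5%, and the fixed sequence holds it there for MAP and HR together. The cost is analysis-plan wording and slightly more programming, with no new data. Fewer individual time points can be called significant. The existing sample size calculation uses "A statistical power of 80% and a one-sided α significance level of 0.05 were used for power analysis with 1:1 allocation" for a yes/no endpoint, so it does not give the power of this contrast; the amendment should say so.

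### A normality check on the trial's own data chooses both the test and the summary for the primary outcome, so the target of inference is not fixed in advance and may differ between time points

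*Protocol article*

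**What the plan says.** The Background of the protocol article defines the endpoint: "The primary outcome is the changes in mean arterial pressure (MAP) and heart rate (HR) at different time points during the surgery". Data collection and Outcome measures list eight times, T0 (baseline) to T7.

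Statistical methods gives a two-branch rule for this endpoint. The first branch reads: "Data from the primary outcome will be presented as mean ± standard deviation if normally distributed, and t-test will be conducted". The second branch applies when the data fail that condition, and changes the summary and the test together: "otherwise, the data will be reported as median (IQR), and no-parametric tests will be performed". The significance criterion is "value < 0.05 was considered significant".

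The article does not say whether the branch is chosen once or separately for each variable and time point. It names no target parameter that would hold in both branches. Sample size estimation does not settle the target either. It works from a binary quantity (in the pilot's traditional group, "50% of patients had a greater than 20% change in blood pressure"), which is neither a mean nor a median of MAP or HR.

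**The concern.** The choice between the branches also changes the question. The t-test compares means. A two-sample rank test compares the tendency of one arm to give larger values than the other, and the article pairs it with medians. Which of these the primary analysis estimates is known only after the data have been inspected.

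The stated hypothesis concerns profiles over time: "hemodynamic profiles will be changed less during gasless vNOTES". If MAP is reported as a mean difference at T3, as medians with a rank test at T4 and as a mean difference again at T5, a reader cannot follow one effect measure along the profile. The change at T4 may reflect a chance departure from normality in one arm and nothing about surgery.

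The switch also gains little. With 49 to 60 patients per arm, a comparison of means does not need normally distributed data.

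**Working it through.** The plan gives no figure for this rule, so there is none to reproduce. Nothing below depends on whether 49 per arm was correctly derived.

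**Inputs from the protocol article**
- Two variables (MAP, HR) at eight times: 2 × 8 = 16 comparisons, or 2 × 7 = 14 without the baseline T0.
- 49 per arm needed and 60 per arm enrolled (Sample size estimation).
- Significance level 0.05, taken as two-sided because Statistical methods does not say.

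**Assumptions**
- Shapiro-Wilk at 5% in each arm; a failure in either arm leads to the Mann-Whitney test, otherwise a t-test (Welch).
- One decision per comparison.
- The distribution shapes named below. The article gives no SD or shape for MAP or HR.

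**Step 1. How often the branch switches when every variable is truly normal**

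Per comparison: 1 − 0.95² = 0.0975.

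At least one switch in k independent comparisons: 1 − (1 − 0.0975)^k = 1 − 0.9025^k.

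| k | Comparisons | Chance of at least one switch |
|---|---|---|
| 7 | one variable, without T0 | 51% |
| 8 | one variable | 56% |
| 14 | both variables, without T0 | 76% |
| 16 | both variables | 81% |

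Simulation with correlated time points gives about 53-59% for mixing within one variable and 77-83% across all 16. Correlation between times should lower these chances, so values above the independence figures of 56% and 81% are best read as simulation noise. In round terms the chances are just over half and about four in five.

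**Step 2. Whether the rule inflates type I error**

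- Same distribution in both arms: the two-stage rule rejects 4.5-5.4% (normal, gamma and lognormal shapes; 49 or 60 per arm).
- Symmetric normal data with unequal SD: the two-stage rule rejects 5.0-5.8% at SD ratios 1.5 to 3. The rank test alone rejects 5.2-5.3% at ratio 1.5, 6.0-6.1% at ratio 2 and 6.8-6.9% at ratio 3.

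There is no material inflation in either case.

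**Step 3. Skew together with unequal spread**

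Lognormal data, 60 per arm. If the means are equal, the median ratio is exp[−(s1² − s2²)/2]. For log-SD 0.3 v 0.2 this is exp[−(0.09 − 0.04)/2] = exp(−0.025) = 0.975.

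| Log-SD | Median ratio at equal means | Two-stage, equal means | Two-stage, equal medians | Welch, equal medians |
|---|---|---|---|---|
| 0.3 v 0.2 | 0.975 | 8.2% | 5.3% | 6.7% |
| 0.3 v 0.15 | 0.967 | 12.1% | 7.7% | 10.0% |
| 0.4 v 0.2 | 0.942 | 17.0% | 6.5% | 13.5% |

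At equal means, Welch rejects 4.8-5.4%. With equal means the rule exceeds 5% because the medians truly differ. With equal medians the ordering reverses, and Welch exceeds 5% because the means truly differ. Neither test is faulty; they answer different questions. With milder spread (log-SD 0.2 v 0.15, or 0.15 v 0.1) at equal means, the rule rejects about 6%.

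**Step 4. Whether means can be used throughout**

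In all equal-mean cases simulated (normal, heavy-tailed, gamma and lognormal; SD ratios 1 to 3; 49 or 60 per arm), Welch's test rejected 4.7-5.6%. Normality is not needed for the mean comparison at this size.

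**The case against.** The strongest defence is that the rule is common, stated in advance, and holds its level when the arms share a distribution. Which normality check and which rank test to use are details that an article may leave to a fuller plan. Both points stand, and the missing details are not the complaint. The complaint is about what the article does state: the data choose the estimand of the primary outcome.

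A second defence is that mixing is not certain. The text can be read as one decision for the whole outcome, and the percentages in step 1 rest on an assumed check applied to each comparison. This also stands. A single decision would remove the mixing, but the data would still decide between means and medians.

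A reader might go further and infer that the rank branch gives false positives whenever only spread differs, since a smaller change under gasless surgery could show as smaller spread. The documents do not support this:
- With symmetric data the excess is slight. The larger rates need skew as well, and they count as errors only for a null of equal means. In that branch the article reports medians, which do differ.
- The Discussion describes a directional mechanism, with pneumoperitoneum raising heart rate and blood pressure. A smaller change may therefore mean a smaller average shift, which either test can detect.
- The Background defines the outcome as changes, and signed changes need not be lognormal.

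**Conclusion.** The point holds as a defect in how the primary analysis is fixed. The data select the test and the effect measure together, and under a per-comparison reading the measure can differ between adjacent time points. The size is just over an even chance of mixing within MAP or HR, and about four in five across both, even with truly normal data. These figures assume a 5% Shapiro-Wilk check in each arm for every comparison, T0 included.

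It is not a finding of inflated type I error. Where skew and unequal spread occur together, the two branches have different nulls, so the conclusion can depend on the branch taken. How often that would arise here cannot be judged, because the article gives no SD or shape for MAP or HR. The change is worth making because it is cheap; the trial does not stand or fall by it.

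**What to change.** Before unblinding, replace the conditional sentence in Statistical methods with a fixed one:
- MAP and HR are compared by the same mean-based method at every time point, whatever a normality check shows. Name one method: Welch's t-test, or a linear model adjusted for the T0 value. With the model, T0 becomes a covariate and is no longer a comparison.
- Report the mean difference with its 95% CI at each time point.
- Give median (IQR) as description only.
- Keep a rank test as a labelled sensitivity analysis that does not decide the result.

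The cost is one sentence, plus the route that Data monitoring sets for any protocol change: agreement of the investigators, submission to the review board and an update of the registry entry. The statistical price is some loss of power against a rank test if the tails are heavy. No more patients or data are needed.
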